### Secondary data linkage plan for primary and secondary outcomes

| Item                                                     | Outcome measurement timing (from the time of enrollment) |          |           |           |
|----------------------------------------------------------|----------------------------------------------------------|----------|-----------|-----------|
|                                                          | 3 months                                                 | 6 months | 12 months | 18 months |
| Hospitalization                            |                                                          |          |           |           |
| Hospitalization date, discharge date                     | ○                                                        | ○        | ○         |           |
| Hospitalization route (outpatient or emergency room)     |                                                          |          |           |           |
| Hospitalization results (discharge or death)             |                                                          |          |           |           |
| Emergency room use                         |                                                          |          |           |           |
| Date (year, month, and date)                             | ○                                                        | ○        | ○         |           |
| Result (discharge, hospitalization, or death)            |                                                          |          |           |           |
| Critical care use                          |                                                          |          |           |           |
| Date of ICU hospitalization (day)                        | ○                                                        | ○        | ○         | ○         |
| Date of ventilator support (day)                         |                                                          |          |           |           |
| Number of CPR attempts                                   |                                                          |          |           |           |
| Hospice use                                |                                                          |          |           |           |
| Hospitalization date, discharge date                     | ○                                                        | ○        | ○         | ○         |
| Death                                      |                                                          |          |           |           |
| Vital status                                             |                                                          |          |           |           |
| Date of death                                            | ○                                                        | ○        | ○         | ○         |
| Cause of death                                           |                                                          |          |           |           |
| Aggressive care use one month before death |                                                          |          |           |           |
| Date of ICU hospitalization (day)                        | ○                                                        | ○        | ○         | ○         |
| Date of ventilator support (day)                         |                                                          |          |           |           |
| Number of CPR attempts                                   |                                                          |          |           |           |
| Direct medical expenses (KRW)              |                                                          |          |           |           |
|                                                          | ○                                                        | ○        | ○         |           |
| Advance care planning status               |                                                          |          |           |           |
| Advance directives                                       |                                                          |          | ○         | ○         |
| Physician orders for life-sustaining treatment           |                                                          |          |           |           |

## 12. Efficacy Endpoint Evaluation Criteria, Methods, and Interpretation

### A. Evaluation Criteria

#### *1) Primary Efficacy Endpoint*

- The proportion of patients with unscheduled hospitalization within 6 months of study enrollment
- Definition of an unscheduled hospitalization: hospitalization at a respective participating institution for acute treatments (excluding scheduled hospitalizations for anti-cancer treatments, operations, and procedures), hospitalization at other medical institutions other than the participating institutions, or **hospitalization of 4 weeks or less at a nursing hospital**

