|                              | 
2. Efficacy Endpoints
 
 
- Primary endpoint: The number of unscheduled hospitalizations within 6 months of study enrollment.
 
* Unscheduled hospitalization: This includes hospitalization at a respective participating institution for acute treatments (excluding scheduled hospitalizations for anti-cancer treatments, operations, and procedures), hospitalization at medical institutions other than the participating institutions, or hospitalization of 4 weeks or less at a nursing hospital.
 
- Secondary endpoint
 
 
n Patient: Medical service use (e.g., hospitalization and ER visit), critical care use (e.g., ICU admission and ventilator support), use of end-of-life medical services (e.g., ICU admission one month before death and ventilator support), satisfaction with the services, quality of life (ESAS and EQ5D), affective disorders (PHQ9), and preparation of advance directives.
 
n Guardian: Satisfaction with the services, quality of life (EQ5D), burden of care (CRA-K), affective disorders (PHQ9), and care competency.
 
n Costs: Medical expenses and care costs
                                                                                                                                                                                                                                                                                                                                                                                                                                                                                                                                                                                                                                                                                                                                                                                                                                                                                                                                                                                                     |

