|----------------------------------------------------------|------------------------------------------------------------------------------------------------------------------------------------------------------------------------------------------------------------------------------------------------------------------------------------------------------------------------------------------------------------------------------------------------------------------------------------------------------------------------------------------------------------------------------------------------------------------------------------------------------------------------------------------------------------------------------------------------------------------------------------------------------------------------------------------------------------------------------------------------------------------------------------------------------------------------------------------------------------------------------|
| Care Goal Setting                                        | Establish care goals at the patient's home based on the assessment results of the patient and guardian (i.e., caregiver). 

- Determine the duration for which the patient wishes to stay at home and the circumstances under which the patient wants to be hospitalized

- Check the patient's and guardian's intention for life-sustaining treatments

                                                                                                                                                                                                                                                                                                                                                                                                                                                                                                                                                                 |

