## **13. Suspension and Dropout Procedures**

### **A. Clinical Trial Suspension Criteria**

- The clinical trial will be suspended in the following cases.

1. When a patient or their caregiver wishes to discontinue the HBMC intervention
2. When a participant passes away
3. When a participant is hospitalized at a medical institution for an additional four weeks
4. When a patient's treatment at the hemato-oncology department of the respective hospital has been terminated or follow-up has been discontinued
5. When a participant uses an inpatient or home-based hospice care services
6. When the suspension of participation in the clinical trial is deemed best for the participant at the investigator's discretion
7. When a participant does not cooperate with the physician in charge of the clinical trial or does not follow the physician's instructions
8. When the regulatory authority, ethics committee, or Institutional Review Board (IRB) suspends the clinical trial

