## **C. Follow-up of Suspended Participants**

- Investigation of the medical records and secondary data linkage will be performed on the suspended participants from the time of suspension to the end of the remaining scheduled follow-up period (18 months after the registration) until no longer possible due to the participant's death, failure to follow-up, or withdrawal of consent. Any case of a patient receiving additional HBMC services (e.g., other HBMC pilot projects) other than the one provided in this clinical trial after the completion of the study will be recorded in the care

reports.

- For participants suspended due to reasons other than death, the follow-up survey will only be conducted with those who consent to participate via a telephone call made by a research nurse.

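### The primary endpoint does not address hospice admissions and, read literally, scores an inpatient hospice stay by where the bed is

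*Protocol*

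**What the plan says.** **Endpoint.** Section 12.A.1 sets the primary endpoint as "The proportion of patients with unscheduled hospitalization within 6 months of study enrollment". Its definition of an unscheduled hospitalisation has three limbs:

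1. "hospitalization at a respective participating institution for acute treatments (excluding scheduled hospitalizations for anti-cancer treatments, operations, and procedures");
2. "hospitalization at other medical institutions other than the participating institutions";
3. "hospitalization of 4 weeks or less at a nursing hospital".

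The Overview (Efficacy Endpoints) repeats the second and third limbs as "hospitalization at medical institutions other than the participating institutions, or hospitalization of 4 weeks or less at a nursing hospital". Hospice appears in neither place.

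**Hospice and follow-up.** Section 13.A lists as suspension reason 5: "When a participant uses an inpatient or home-based hospice care services". Outcome collection does not stop there. Section 13.C says "Investigation of the medical records and secondary data linkage will be performed on the suspended participants", and the Overview's Suspension Criteria say the same for reason 5. Section 13.D treats dropout as withdrawal of consent, which is a different matter from suspension.

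**Hospice data.** The linkage table in section 11.C lists hospice admission and discharge dates as an item separate from hospitalisation. Nothing connects that item to the primary endpoint. The medical-record survey in section 11.B has no hospice item.

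**The concern.** The condition on acute treatment is attached to the first limb only. Two patients with the same planned hospice stay can therefore be scored differently, one an event and the other not, solely because one bed is in the trial hospital and the other is not.

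That would be mere noise if location were unrelated to arm. Here each arm is three named hospitals, so any difference in hospice placement between the two sets is carried into the treatment comparison. The protocol suggests two routes to imbalance, which point in opposite directions:

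- **Against control.** The Overview waives the home-visit distance exclusion for the control group (section 5.B does not repeat the waiver). Control patients may therefore live farther away and use a hospice near home, which would count as an event.
- **Against HBMC.** The HBMC care plan (section 9.B.4) covers "the circumstances under which the patient wants to be hospitalized" and intentions on life-sustaining treatment. If this raised hospice entry, each outside hospice bed would count against HBMC.

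Both are inferences. They show why the rule should be fixed before data are seen, but not which way a bias would go.

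**Working it through.** **1. Reading the limbs against one planned inpatient hospice stay**

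| Place of stay | Condition in the definition | Score |
|---|---|---|
| Patient's own trial hospital | must be for acute treatment | naturally not an event, but hospice is not named, so this is an inference |
| Another medical institution | none | event |
| Nursing hospital | 4 weeks or less | event if short |

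An unplanned symptom crisis admitted to an in-house hospice bed could be classed as acute. So the in-house score is open to the assessor, while the outside score is not.

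**2. The plan's own power figure**

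Inputs from section 6: 198 per arm, three clusters of 66, ICC 0.015, alpha 0.05 (two-sided assumed), effect size 0.2, stated power 0.83007. The base rate is not given. I assume 50% vs 30%.

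- Design effect = 1 + (66 − 1) × 0.015 = 1.975.
- Effective n per arm = 198 / 1.975 = 100.25.
- Power = Φ[(d − 1.96 × SE0) / SE1], with d = 0.20, pooled SE0 = 0.0692 and unpooled SE1 = 0.0677. This gives 0.829, in agreement with 0.830.

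With the only event counts that section 6 prints (40/198 vs 20/198), the same formula gives 0.514. The match thus depends on the assumed base rate. The wording problem does not.

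**3. Artificial difference from location scoring**

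Let h be the share of each arm whose only candidate event is an inpatient hospice admission within 6 months, and s the share of those stays at other institutions. Location scoring adds h × s to the arm's event rate, so

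artificial difference = h × (s_control − s_HBMC).

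The protocol gives neither h nor s. Assumed: h = 5, 10, 15%, and s = 80% in one arm and 20% in the other.

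*No true effect, 30% in both arms, s = 80% control, 20% HBMC:*

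| h | Control rate | HBMC rate | Artificial difference | Rejection at nominal 5% |
|---|---|---|---|---|
| 5% | 34% | 31% | 3 points | about 7% |
| 10% | 38% | 32% | 6 points | about 14% |
| 15% | 42% | 33% | 9 points | about 26% |

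*True 50% vs 30%, split reversed (20% control, 80% HBMC):*

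| h | Control rate | HBMC rate | Observed difference | Power |
|---|---|---|---|---|
| 5% | 51% | 34% | 17 points | about 0.69 |
| 10% | 52% | 38% | 14 points | about 0.51 |
| 15% | 53% | 42% | 11 points | about 0.34 |

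*Equal s in both arms, or one rule for every bed:* at equal h the artificial difference is h × 0 = 0, and power stays at 0.81 to 0.83.

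**The case against.** - **Separate tracking.** The linkage table and the Overview list hospice apart from hospitalisation, which may mean that hospice stays were never meant to count. This is fair but not decisive: ICU stays are also listed separately, and the definition itself contains no such exclusion.
- **No stated frequency.** A reader might infer that hospice is an expected exit from the intervention. The text does not support that. It is one of eight suspension reasons, no rate is given, and entrants are on or planning cancer treatment, ECOG 1 or 2, with no current or prior hospice use. That HBMC raises hospice entry is conjecture too, since the care plan does not mention hospice.
- **No stated location.** A reader might picture one arm sending every hospice patient out and the other keeping all in-house. The protocol does not say which of the six hospitals have hospice beds, so that is an extreme case. Patients with an earlier unscheduled admission are also unaffected, because the endpoint is binary.
- **A wider asymmetry.** The second limb counts any outside admission, scheduled or not, and hospice is one instance. This stands: a hospice rule does not cure the rest.
- **Left to the SAP.** Detailed event classification often is. But this definition is fixed in the protocol, and as fixed it depends on location.
- **Ascertainment.** Linkage needs consent, and section 11.C words it for the intervention group, whereas the Overview does not limit it by arm. If hospice stays were recognised mainly in linked HBMC patients, exempting them would remove events from that arm only. This stands and shapes the fix.

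**Conclusion.** The point holds in a limited form. The definition leaves hospice unaddressed. By its wording, a hospice admission at another institution is an event, while the same planned stay in-house would naturally not be. The second half is an inference. It would go too far to say that there is no scoring rule at all: the general definition supplies one by location, and what is missing is a rule for hospice.

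Since follow-up continues after suspension for hospice and arms are fixed sets of hospitals, this can bias the primary comparison. Neither size nor direction can be established from the protocol. The 3 to 9 points rest wholly on the assumed 5 to 15% hospice share and 80%/20% split, and the bias is zero if location is balanced. It should be settled before outcomes are examined.

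**What to change.** - **One rule.** State in section 12.A.1 and the Overview how an inpatient hospice admission is scored, the same at every institution. An example would be that it is not an unscheduled hospitalisation wherever it occurs. Counting it everywhere would be equally uniform.
- **Sensitivity analysis.** Repeat the primary analysis under the opposite rule, and report hospice entry within 6 months by arm.
- **Same ascertainment in both arms.** Add a hospice item to the medical-record survey in section 11.B. Reconcile section 11.C (linkage worded for the intervention group) with the Overview (not limited by arm).

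This changes scoring and data capture only, not patient care. The cost is a sentence in two places, one more record item and the reconciliation of the linkage text. If hospice is exempted, there will be somewhat fewer events, and hospice entry may displace later acute admissions. The opposite-rule analysis and the by-arm hospice report would show how far that matters.

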#### *2) Secondary Efficacy Endpoint*

- Domain 1: The secondary endpoints related to patients' use of medical services and critical care are described below.
  - Number of unscheduled hospitalizations within 6 months of study enrollment (continuous or count variable)
  - Length of hospitalization (total length of hospitalization; continuous variable)
  - History of hospitalization (dichotomous variable)
  - Number of ER visits (continuous variable)
  - Length of ICU hospitalization (total length of hospitalization; continuous variable)
- Domain 2: The secondary endpoints related to patients' quality of life and their satisfaction with the service are described below.
  - Patient's quality of life (EQ-5D; continuous variable)
  - Patient's degree of symptom control (ESAS; continuous variable)
  - Patient's emotional status (PHQ-9; continuous variable)

- Patient's satisfaction with the service (continuous variable)
  
- Domain 3: The secondary endpoints related to the patient's death and preparation of advanced directives are described below.
  - Survival after enrollment (days; continuous variable)
  - Length of ICU hospitalization within 1 month of the patient's death (total length of hospitalization; continuous variable)
  - History of anti-cancer treatment within 1 month of the patient's death (dichotomous variable)
  - Duration of ventilator support within 1 month of the patient's death (total number of days; continuous variable)
  - Preparation of advance directives or physician orders for life-sustaining treatment (dichotomous variable)
  
- Domain 4: The secondary endpoints related to guardians' quality of life and their satisfaction with the service are described below.
  - Guardian's quality of life (EQ-5D; continuous variable)
  - Guardian's emotional status (PHQ-9; continuous variable)
  - Guardian's burden of care (CRA\_K; continuous variable)
  - Guardian's care competency (continuous variable)
  - Guardian's satisfaction with the service (continuous variable)
  
- Domain 5: The secondary endpoints related to medical expenses are described below.
  - Direct medical expenses (continuous variable; KRW)
  - Indirect medical expenses (continuous variable; KRW)

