| Hypotheses                                                     | 
 
1. Use of medical services, such as unscheduled hospitalizations and emergency room (ER) visits, will be significantly reduced among advanced cancer patients who receive home care education and participate in the HBMC intervention program as compared to the patients in the control group.
 
2. The quality of life (QoL) will be significantly higher, and the degree of symptom control will be significantly better among advanced cancer patients who receive home care education and participate in the HBMC intervention program than those in the control group.
 
3. The rate of establishing advance care planning will be significantly higher among advanced cancer patients who receive home care education and participate in the HBMC intervention program than those in the control group.
 
4. The mortality rate will be significantly lower among advanced cancer patients who receive home care education and participate in the HBMC intervention program than those in the control group.
 
 |
| Basis of the Study                                             | 
 
- The provision of home care environment-based intervention to patients with severe illnesses can significantly reduce readmission rates and improve survival rates compared to the provision of existing hospitalization and outpatient services (Malik et al., 2019).
 
- Symptom control is better when home-based palliative care services are provided to cancer patients (Gomes et al., 2013).
 
                                                                                                                                                                                                                                                                                                                                                                                                                                                                                                                                                                                                                               |

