|                    | 
discontinued
 
 
5. When a participant uses an inpatient or home-based hospice care services
 
6. When the suspension of participation in the clinical trial is deemed best for the participant at the investigator's discretion
 
7. When a participant does not cooperate with the physician in charge of the clinical trial or does not follow the physician's instructions
 
8. When the regulatory authority, ethics committee, or Institutional Review Board suspends the clinical trial
 
 
* The termination of the study for patients who discontinue the study is as follows.
 
 
- Reasons 1, 3, 4, 5, 6, 7, or 8: Continuation of the investigation of medical records and secondary linkage data (18 months) until 12 months after the enrollment or withdrawal of consent; the additional survey will be conducted only with the patient's consent
 
- Reason 2: Survey or investigation of medical records will not be possible until 12 months after the enrollment; secondary data linkage will be conducted
 
 
* When participation consent is withdrawn, the previously collected data of the patient will be discarded if the patient does not wish the data to be used in the study.
                                                                                                                                                                                                                                                                                                                                                                                                                                                        |

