### ***2) Secondary Efficacy Endpoint***

- When the means of the continuous variables in the intervention and control groups differ at a significance level of 0.05 or less, it will imply that the HBMC intervention was effective for the secondary endpoint.

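### Three end-of-life endpoints exist only for decedents and follow-up quality of life only for patients alive, yet the protocol compares the groups on them and reads a significant difference in means as effectiveness

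*Protocol*

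**What the plan says.** **Endpoints that need a death.** Domain 3 in section 12.A.2 has five items. Three are confined to decedents: "Length of ICU hospitalization within 1 month of the patient's death (total length of hospitalization; continuous variable", "Duration of ventilator support within 1 month of the patient's death (total number of days; continuous variable" and "History of anti-cancer treatment within 1 month of the patient's death (dichotomous variable". The other two, survival and advance directives, cover all patients.

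**Endpoints that need a living patient.** Domain 2 includes EQ-5D, ESAS and PHQ-9. Section 11.A collects them by questionnaire at enrolment, 3 months and 6 months. For participants who have died, the Overview (Suspension Criteria) states: "Survey or investigation of medical records will not be possible until 12 months after the enrollment".

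**Comparison and reading.** Section 12.B.2 compares group means or proportions for each item in Domains 1 to 5. Section 12.C.2 says that when continuous means differ at the 0.05 level, "it will imply that the HBMC intervention was effective for the secondary endpoint". The Overview (Statistical Analysis) adds regression with correction for baseline differences, and section 14.B.4 adds GEE, with Kaplan-Meier and Cox for survival.

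**Hypotheses (Overview).** Hypothesis 2: "The quality of life (QoL) will be significantly higher, and the degree of symptom control will be significantly better". Hypothesis 4: "The mortality rate will be significantly lower among advanced cancer patients" who receive HBMC. Neither gives a size.

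**Death in the analysis rules.** The intention-to-treat statements settle which group a patient belongs to. The rule on incomplete data covers withdrawal and dropout and does not name death.

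**The concern.** If HBMC changes who dies, as hypothesis 4 supposes, the decedents in the two groups are different kinds of patient, and so are the survivors. A difference in ICU days among decedents, or in EQ-5D among those alive, can then arise although HBMC changed neither outcome in any patient. Hypotheses 2 and 4 also pull against each other: if frailer patients are kept alive, mean quality of life among those alive falls.

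The look-back is a second, separate problem. Patients enter while receiving or planning cancer treatment, and the first home visit may come up to two weeks after enrolment. For a death in the first month, the one-month window reaches back before enrolment and records care that HBMC could not have influenced.

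At stake is the claim that HBMC makes end-of-life care less aggressive or improves quality of life. The primary endpoint is not affected.

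**Working it through.** **1. Who enters each comparison**

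| Endpoint | Defined for | Under section 12.C.2? |
|---|---|---|
| ICU days, last month of life | decedents | yes (continuous) |
| Ventilator days, last month of life | decedents | yes (continuous) |
| Anti-cancer treatment, last month of life | decedents | no (dichotomous); compared under 12.B.2 |
| EQ-5D, ESAS, PHQ-9 at 3 and 6 months | patients alive | yes (continuous) |
| Survival; advance directives | all enrolled | not at issue |

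The structural point follows from this table and hypothesis 4. It needs no figure, and the plan states none to reproduce. The sizes below rest on assumptions.

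**2. ICU use among decedents, with no HBMC effect on ICU use**

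Assumed: severity S is standard normal; a patient dies if a latent variable correlated r with S lies in its upper tail; logit P(ICU if dying) = -1.4 - 0.7 S, so sicker patients get less ICU care. Mortality is 50% in control and 40% with HBMC. Results by simulation:

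- r = 0.5: 17.5% v 16.7%, a difference of -0.8 points.
- r = 0.8: 14.8% v 13.6%, a difference of -1.2 points.

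Deaths are 0.50 × 198 = 99 and 0.40 × 198 = 79. Ignoring clustering, SE = sqrt(p0(1-p0)/99 + p1(1-p1)/79), which is 5.7 and 5.3 points. The bias is 0.8/5.7 = 0.14 and 1.2/5.3 = 0.23 of a standard error.

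With the coefficient changed to +0.7 (sicker patients get more ICU care), the same model gives 26.3% v 27.4% and 29.0% v 30.8%. The bias now runs against HBMC.

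**3. A second model, for anti-cancer treatment in the last month**

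Here frailty raises the risk of death and lowers the chance of late treatment. With control mortality of 30-60% and hazard ratios of 0.7-0.9, the proportion shifts by -0.2 to -0.8 points if the hazard ratio is uniform, and by -0.9 to -3.1 points if only the less frail half benefits.

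**4. Worst-case limit**

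Suppose HBMC only prevents deaths, control mortality is 40% and the hazard ratio is 0.8. HBMC mortality is 1 - 0.6^0.8 = 0.335, so 0.335/0.40 = 83.9% of control deaths would also have occurred under HBMC. An observed control rate of 30% is then compatible, in that comparable subset, with anything from (0.30 - 0.161)/0.839 = 16.5% to 0.30/0.839 = 35.8%. This is a limit, not an expected size.

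**5. EQ-5D among those alive, with no HBMC effect on any patient's quality of life**

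Assumed: mean 0.70, SD 0.25, correlation 0.5 between severity and worse EQ-5D, mortality 35% v 25%.

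- Among those alive, the HBMC mean is 0.009 lower (r = 0.5) or 0.015 lower (r = 0.8).
- SE = 0.25 × sqrt(1/128.7 + 1/148.5) = 0.030, where 128.7 = 0.65 × 198 and 148.5 = 0.75 × 198.
- With all enrolled patients counted and death set to 0, the HBMC mean is 0.065 to 0.067 higher.

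A wider grid (control mortality 10-40%, hazard ratio 0.7-0.9, correlation 0.4-0.7) gives -0.004 to -0.07 SD among those alive.

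**6. Composite in all enrolled: died with ICU use in the last month**

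This is mortality times the rate among decedents in step 2, unrounded:

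- r = 0.5: 8.73% v 6.66%, a relative fall of 24%.
- r = 0.8: 7.40% v 5.45%, a relative fall of 26%.

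Both falls come almost wholly from the assumed mortality difference.

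**7. Look-back**

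With a 30-day window, a death on day 10 has 30 - 10 = 20 days before enrolment, or two-thirds of the window.

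**The case against.** - **The bias is small.** On these figures it is well under half a standard error. For EQ-5D it works against HBMC, so a false favourable result becomes less likely. This stands. A reader might infer that selection will produce a false reduction in aggressive care. The documents do not support that: they give no mortality figure, and the ICU direction turns on an assumed relation.
- **The EQ-5D sign reversal is not evidence of bias.** The all-enrolled gain of about 0.065 is roughly the 10-point mortality difference times a mean index of 0.65 to 0.70. It restates survival in another estimand. This stands.
- **All-patient measures exist.** Domain 1 lists ICU days without a death condition, and the Overview lists critical care use, including ventilator support, apart from end-of-life use. A reader might infer that the plan has no all-enrolled critical-care comparison. That would be wrong.
- **The effectiveness rule is narrower than it looks.** Section 12.C.2 speaks of continuous means, so the anti-cancer treatment item is outside its wording. The rule still reaches the other two decedent items and the three patient scales.
- **Adjustment and an unseen SAP may deal with it.** Baseline adjustment does not in general remove selection on an event after enrolment. An SAP may define how death is handled, but the reading in section 12.C.2 would remain in the protocol. This objection fails in part.
- **Early deaths should be few.** Eligibility is ECOG 1 or 2 and excludes patients judged too unwell and those who have used hospice services. The look-back rule is also the same in both groups. This limits the size, which cannot be estimated from the protocol, but the definition still counts care given before HBMC.

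**Conclusion.** The point holds as a fault in a stated reading rule, not as a complaint about missing detail. Under the protocol's own hypothesis 4, the decedent-only and alive-only contrasts compare groups selected after enrolment, and significance in them does not by itself show that HBMC works.

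The size is modest. Under assumed mortality it is about 1 percentage point for ICU use among decedents, in either direction, and about 0.01 on EQ-5D, against HBMC. The anti-cancer treatment item could move by up to about 3 points if the survival benefit fell only in less frail patients. The look-back fault is definitional and needs no assumption.

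The stronger reading, that these endpoints would be seriously misleading or that the trial's main result is at risk, is not supported. Severity: minor, secondary endpoints only.

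**What to change.** 1. In sections 12.B.2 and 12.C.2, present the three decedent-only endpoints as descriptive, and label EQ-5D, ESAS and PHQ-9 results as *among patients alive*. Exclude both sets from the rule that significance implies effectiveness, and report them beside the survival analysis.
2. For the between-group comparison of critical care, use the all-patient ICU days already in Domain 1 and ventilator use as listed in the Overview, over a fixed period from enrolment. If a composite of dying with ICU care, ventilation or anti-cancer treatment in the last month is added, read it together with mortality and not as evidence of less aggressive care, because a mortality difference alone moves it.
3. Start the one-month look-back no earlier than enrolment.
4. Beside the EQ-5D result among those alive, add a supplementary all-enrolled analysis with the index at 0 from death, stated to combine survival and quality of life. Apply it at 3 months. Apply it at 6 months only once the control-group data are reconciled: the section 11.A table marks 6-month EQ-5D for the intervention group only, the section 11.A text includes both groups, and the Overview includes controls who consent.

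Cost: wording changes and one extra analysis, with no new data collection at 3 months. The end-of-life endpoints will carry weaker claims, and early deaths will contribute a shorter window.
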